### Inclusion and exclusion criteria

The following inclusion criteria are listed: (1) eyes with POAG, defined as an open angle on gonioscopy and structural loss detected by optic coherence tomography (OCT) and/or functional loss observed with visual field examination, (2) age between 40 and 80 years, (3) visual field mean deviation ≥  − 12 dB, (4) retinal nerve fiber layer thickness (RNFLT) ≥ 60 µm, (5) previous uneventful cataract surgery with intraocular lens implantation, (6) best corrected visual acuity (BCVA) ≥ 0.1 at the Snellen chart (LogMAR = 1), (7) IOP ≥ 18 mmHg measured in two occasions with the Goldmann applanation tonometer under a maximum of 3 IOP-lowering medications, and (8) IOP between 20 and 36 mmHg after medication washout.

Exclusion criteria are defined as: (1) secondary open-angle glaucoma (uveitis, corticoid-induced, pseudoexfoliation, pigmentary and juvenile), (2) primary or secondary angle-closure glaucomas, (3) phakic eyes or cataract surgery performed less than 30 days before inclusion, (4) previous glaucoma surgery (other MIGS procedures, glaucoma drainage devices, or cyclophotocoagulation), (5) previous vitreoretinal surgery, and (6) severe corneal opacity.

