**Fig. 1 Fig1:**
[figure not shown]
Study flow chart. BANG, bent Ab interno needle goniotomy; GATT, gonioscopy-assisted transluminal trabeculotomy; IOP, intraocular pressure; RNFLT, retinal nerve fiber layer thickness; mGCL, macular ganglion cell layer; BMO-MRW, Bruch’s membrane opening – minimum rim width; MD, visual field mean deviation; ECD, endothelial cell density; NEI-VFQ-25, National Eye Institute Visual Field Function Questionnaire 25

At baseline, a complimentary evaluation will be done, including ultrasonic pachymetry and specular microscopy (Tomey EM3000, Tomey Corporation, Japan) to measure central corneal thickness and endothelial cell density, respectively; RNFLT, macular ganglion cell layer and Bruch’s membrane opening — minimum rim width measurements are obtained with OCT (Spectralis OCT, Heidelberg Engineering, Germany) for structural evaluation; 24–2 visual field tests using SITA-Fast (Humphrey Field Analyzer, Carl Zeiss Meditec AG, Germany) for functional evaluation; and quality of life assessment with the Brazilian validated version of the National Eye Institute—Visual Function Questionnaire-25 questionnaire [25].

After meeting all inclusion criteria at recruitment, patients will be invited to participate in the study. All procedures will be fully explained and an informed consent will be obtained by one of the three members of the research team. After that, patients will be asked to interrupt the use of all IOP-lowering medications and return after 30 days to measure the IOP. The IOP measured after medication washout will be considered the baseline IOP.

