### Follow-up

Patients will be followed 1, 7, 15, 30, 60, 90, 180, 330, and 360 days after surgery (Table 1). In all visits, BCVA and IOP will be measured. Additional visits may be scheduled at the surgeon’s discretion. If in two consecutive visits, the IOP is higher than 18 mmHg, a topical carbonic anhydrase inhibitor will be introduced; if IOP remains above 18 mmHg, the introduction of a second-class IOP-lowering medication will be considered. At visit 330, a new medication washout will be done, and patients will be instructed to interrupt all medications in the operated eye until visit 360.

**Table 1 Tab1:** Procedures at each timepoint

	**Enrolment**	**Allocation**	**Post-allocation**						**Close-out**
Timepoint**	*** − t***_***1***_	**0**	***t***_***1***_	***t***_***2***_	***t***_***3***_	***t***_***4***_	***t***_***5***_	***t***_***6***_	***t***_***7***_
Description	*** − 30 days***	**0**	***1DPO***	***7DPO***	***30 DPO***	***90 DPO***	***180 DPO***	***330 DPO***	***360 DPO***
Enrolment									
* Eligibility screen*	X								
* Informed consent*	X								
* Allocation*		X							
Interventions									
* Surgery (GATT)*		X							
* Surgery (BANG)*		X							
Assessments									
* Intraocular pressure*	X		X	X	X	X	X	X	X
* Medication use*	X		X	X	X	X	X	X	X
* Functional, structural, and quality of life evaluation*	X				X	X	X		X
* Adverse effects*			X	X	X	X	X	X	X

*DPO* Day postoperative, *GATT* Gonioscopy-assisted transluminal trabeculotomy, *BANG* Bent ab interno needle goniotomy

At visits 30, 90, 180, and 360, all exams obtained at baseline for structural, functional, and quality of life assessment will be repeated. After completing the study endpoint, patients will continue the regular follow-up at the two glaucoma centers enrolled in this study.

During the follow-up period, the investigators will be in close contact with participants (telephone and/or message) to assess any change in visual status. If any change is referred by the participant, a visit will be scheduled for re-evaluation.

Participants will be allowed to withdraw from the study at any time without justification. If possible, patients will be asked to attend for a visit 12 months after surgical intervention to evaluate IOP. Patients who decide to withdraw from the study will be allowed to continue the regular follow-up at the Glaucoma Sector of the recruiting centers without any prejudice.

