### Statistical analysis plan

The normality of the data will be assessed by the Shapiro–Wilk test. Comparison of longitudinal changes in IOP or the number of medications within a group will be done by Student’s paired *t*-test or the Wilcoxon rank sum test depending on the distribution of the data. The comparison of the above-mentioned parameters between the groups will be done by a non-paired Student’s *t-*test or the Mann–Whitney-*U* test depending on the distribution of the data. Categorical variables will be compared using the chi-square or the Fisher exact test.

A Kaplan–Meier survival curve will also be used to compare the success rates of both procedures. Complete success is defined as an IOP reduction ≥ 20% from baseline under no antiglaucoma medication at the final 12-month visit. Qualified success is defined as an IOP reduction ≥ 20% from baseline with the use of medication, but no increase in medication compared to the recruitment visit. Failure is defined as an IOP reduction < 20% from baseline, the need of additional glaucoma surgery to control IOP, IOP < 5 mmHg with the evidence of hypotony maculopathy, or persistent BCVA equal or lower to light perception. The log-rank test will be used to compare the survival curves of both procedures. *P* values < 0.05 will be considered statistically significant.

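### The success categories do not fit the two washouts: drops alone can give a qualified success before day 330, and at month 12 drug status separates no adherent eye

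*Protocol article*

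**What the plan says.** All references are to the protocol article.

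- **Baseline** (Participant recruitment, initial procedures, and randomization). All drops are stopped for 30 days before surgery, and the pressure read at the end of that period is the reference for every later comparison: "The IOP measured after medication washout will be considered the baseline IOP".
- **Eligibility** (Inclusion and exclusion criteria). The recruitment requirement is "IOP ≥ 18 mmHg measured in two occasions", and the treatment allowed when those readings are taken is limited by the words "under a maximum of 3 IOP-lowering medications". The baseline requirement is "IOP between 20 and 36 mmHg after medication washout".
- **Drops during follow-up** (Follow-up). One drug class is started after two consecutive visits above 18 mmHg, and a second class is considered if the pressure stays above that level.
- **Second washout** (Follow-up). At day 330, "patients will be instructed to interrupt all medications in the operated eye", and this lasts until day 360, the close-out visit in Table 1.
- **Success** (Statistical analysis plan). Complete success is a fall of at least 20% from baseline "under no antiglaucoma medication at the final 12-month visit". Qualified success is the same fall "with the use of medication, but no increase in medication compared to the recruitment visit"; no visit is attached to it. Failure is a fall below 20%, further glaucoma surgery, hypotony maculopathy with IOP below 5 mmHg, or persistent vision at or below light perception. Success is compared by Kaplan-Meier curves and a log-rank test.

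**The concern.** The Discussion presents the two washouts as the means of seeing the surgical effect without the influence of medication. The success categories do not follow that design in three respects.

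1. Qualified success takes a pressure on drops and measures it against a baseline off drops. Its only limit on drugs is the count at recruitment, so the effect of the drops is credited to the procedure.
2. At month 12, drug status is set by the protocol and not by the eye's need. The clause meant to separate complete from qualified success separates nobody who adheres.
3. The categories do not cover every eye.

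At stake is the comparison of success between the two procedures. As written, the analyst has to choose the visit and the meaning of medication status after the data exist, in a trial whose investigators are not masked.

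**Working it through.** The article states no figure for this point, so there is none to reproduce. The check uses the eligibility limits and the visit timing.

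**Step 1: drops alone, before day 330.** Let B be the washed-out baseline (20 to 36 mmHg) and M the IOP at recruitment on drops (at least 18 mmHg). If surgery does nothing and drops bring the eye back to M, the fall from baseline is 1 − M/B. It meets the criterion when M ≤ 0.8 × B. With M at its lowest permitted value, this needs B ≥ 18/0.8 = 22.5 mmHg.

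| B (mmHg) | 20% target, 0.8 × B | Fall with M = 18, no surgical effect | Meets 20%? |
|---|---|---|---|
| 20 | 16.0 | 1 − 18/20 = 10% | no |
| 22 | 17.6 | 1 − 18/22 = 18.2% | no |
| 22.5 | 18.0 | 1 − 18/22.5 = 20% | yes |
| 25 | 20.0 | 1 − 18/25 = 28% | yes |
| 30 | 24.0 | 1 − 18/30 = 40% | yes |
| 36 | 28.8 | 1 − 18/36 = 50% | yes |

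A less extreme eye has M = 20 on two drugs and B = 26: (26 − 20)/26 = 23.1%, a qualified success with no surgical effect.

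The article gives no drop effect, so I take a range. At 10% or 15% the eye does not qualify on drops alone; at 20%, 25%, 30% or 35% it does. If surgery lowers IOP by a fraction s and the effects multiply, drops need to add 1 − 0.8/(1 − s):

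- s = 0.10: 1 − 0.8/0.90 = 11.1%
- s = 0.15: 1 − 0.8/0.85 = 5.9%

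**Step 2: month 12.** Drops in the operated eye stop at day 330, and the final visit is day 360.

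- Every eye that follows the washout is off drugs at day 360, so all of them meet the no-medication clause.
- For the same reason, none of them can be a qualified success at that visit.
- The eye with B = 26 and 20 mmHg on drops at day 330 is qualified then (23.1%). With no surgical effect it returns to 26 mmHg off drops: (26 − 26)/26 = 0%, a failure. The eye has not changed; the schedule has removed its drops.
- An eye on drops up to day 330 with B = 30 and 24 mmHg at day 360 has (30 − 24)/30 = 20%. It is a complete success, in the same class as an eye that never needed drops.

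**Step 3: coverage.** Take an eye recruited on one drug, with B = 30, that reads 24 mmHg on two drugs at a visit before day 330. Its fall is 20%. It is not complete (on drugs), not qualified (more drugs than at recruitment) and not a failure (the fall is not below 20% and no other failure criterion is met). It has no category.

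**The case against.** The strongest case on the other side has four parts.

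- **These categories are not the main result.** This stands. The Setting section names IOP reduction as the primary outcome and does not list success among the secondary ones. A reader might infer that the trial's principal finding is compromised; the documents do not support that.
- **Inflation is not shown.** This stands too. A reader might infer that success is inflated in both arms and the difference between procedures diluted. But if success is judged at month 12, an eye carried by drops fails once they are withdrawn, so drops mainly delay its failure on the curve. If qualified success is judged earlier, inflation is possible. The article does not say which applies, and it gives nothing from which to count the eyes affected.
- **Complete success at month 12 is coherent.** This stands. A fall from 30 to 24 mmHg, both washed out, is a true unmedicated 20% reduction, which the second washout is meant to measure. It is not drug contamination. What remains is that the complete and qualified categories cannot be told apart at that visit.
- **The recruitment drops are not simply resumed.** This stands as a limit. The Follow-up section describes its own sequence of up to two classes, so a return to exactly the recruitment IOP is an assumption. It also means that, under the steps described, exceeding the recruitment count needs an eye recruited on no drug or one.

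None of this answers the mismatch itself: a medicated pressure against an unmedicated baseline, no visit for qualified success, and an eye with no category.

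**Conclusion.** The definitions are wrong as written and need to be reconciled with the baseline and Follow-up sections. Before day 330, drops alone can produce a qualified success over baselines of 22.5 to 36 mmHg within the eligible 20 to 36. This assumes at least one drug at recruitment, a drop effect of 20% or more if surgery does nothing, and a postoperative drop effect no larger than the one at recruitment. At day 360 the qualified category is empty for every eye that follows the washout; eyes that do not follow it, or are put back on drops, are the exceptions, and the article does not say how to classify them. Eyes with an adequate fall on more drugs than at recruitment are unclassified.

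The damage is confined to the Kaplan-Meier and log-rank success comparison. The net bias cannot be signed or sized from the article: counting the drop effect adds successes, while withdrawing drops at day 330 adds failures.

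**What to change.** Judge the 20% criterion only on the washed-out day-360 IOP against the washed-out baseline, and use drug status at day 330, before the washout, to separate the categories:

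- **Complete:** fall of at least 20%, and no drugs at day 330.
- **Qualified:** fall of at least 20%, on drugs at day 330, and no more drugs than at recruitment.
- **Failure:** every other eye, including those on more drugs than at recruitment and those meeting any other listed failure criterion.

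Say explicitly that an eye on drops at day 360 falls under failure, or give another rule for it. An eye with no day-360 measurement is a missing-data question that this wording does not settle.

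Compare the day-360 proportions with the chi-square or Fisher test already planned. In the survival curve, do not count an on-drug IOP before day 330 as meeting the 20% criterion against the washed-out baseline, and state how such visits are handled.

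Two eyes test the rule, both with baseline 30 and recruitment 24 mmHg on two drugs:

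- One drug and 20 mmHg at day 330, then 24 off drugs at day 360: (30 − 24)/30 = 20%, qualified.
- Two drugs and 19 mmHg at day 330, then 25 off drugs: (30 − 25)/30 = 16.7%, failure.

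Each lands in exactly one category. Setting the day-330 IOP against the recruitment IOP for qualified success, which may look like the natural comparison, does not manage this. The first eye shows (24 − 20)/24 = 16.7% and is left without a category. The second shows (24 − 19)/24 = 20.8% and is both qualified and a failure.

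The cost is small. IOP and medication use are already collected at recruitment, day 330 and day 360. The survival analysis needs a short rewording, qualified success rates will probably be lower, and because recruitment is under way the change should be documented before outcome data are compared by arm.

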### Dissemination plans

The results of the study will be presented in ophthalmology meetings and submitted to indexed scientific journals. Authorship eligibility will follow the ICMJE guidelines [27].

## Discussion

### Strengths

Our study provides a standardized protocol that could be used for future studies on MIGS. The strengths of our protocol rely on its single-masked and randomized design. Although several studies on MIGS and goniotomy have been published [11–23], this is, to the best of our knowledge, the first RCT that directly compares those two different standalone trabecular MIGS.

The design of our protocol presents several advantages when compared to the previously published studies evaluating goniotomy-like procedures [11–23]. First, the nature of an RCT reduces the selection bias observed in retrospective studies; moreover, our study will only include patients with previous successful cataract surgery. Phacoemulsification alone is known to promote 13% and 12% reductions in IOP and the number of medications in POAG eyes, respectively [28]. Since previous studies [11–23] mixed standalone and combined procedures, it was not possible to determine the real effectiveness of MIGS on the reduction of IOP and medications. Also, glaucomas other than POAG will not be included in our study. Although some other types of glaucoma are classified as open angle (pigmentary, pseudoexfoliative, corticoid-induced), their pathophysiology is different and the results of surgical procedures may also vary. The inclusion of mild to moderate glaucoma allows MIGS that aim at Schlemm’s canal to achieve target IOP. In severe glaucomas, which typically require low target IOPs, the trabecular meshwork biomechanical pump for aqueous humor outflow is compromised, which may also lead to Schlemm’s canal and collector channels collapse [10], which could influence the success of the goniotomy. Finally, the medication washout before the procedure and at the end of the follow-up will allow to verify the real efficacy of the procedures without the influence of compliance to medical treatment and without the different effects of IOP-lowering medications.

Although our study was designed to compare two goniotomy-like procedures, its design can be expanded to compare other MIGS techniques. The protocol provides a well-established 1-year postoperative follow-up, which is also verified in major glaucoma trials [29–31]. Moreover, it is not limited to IOP control and investigates other parameters, such as functional and structural evaluation, which are important to define glaucoma progression [2], safety (ECD), and patients’ quality of life.

One major barrier for the wider application of MIGS in ophthalmology is the costs involved [32, 33]. Some of the MIGS aiming at Schlemm’s canal are costly, including the Trabectome (Neomedix Inc., Tustin, USA) [26], KDB [34], Hydrus (Ivantis, Inc, Irvine, USA) [35], and iStent (Glaukos Corporation, Laguna Hills, USA) [36]. This limits the utilization of such techniques in developing countries. On the other hand, BANG and GATT are low-cost MIGS. Both techniques require a surgical gonio lens and an additional suture wire or needle, which are low cost [32, 33]. In Brazil, the average cost of a 5–0 Prolene wire used in GATT is around USD 3.00, while a 25-G needle used in BANG costs around USD 0.02. On the other hand, KDB has an estimated cost of USD 400, while iStent, USD 1000. At the time, there are no prospective studies comparing BANG to other MIGS or traditional glaucoma surgeries. Because of the low cost of both procedures, the results of this study could serve as a basis for ophthalmologists of developing countries to choose the type of goniotomy-like procedure they prefer.

### Limitations

Our study has some limitations. Although the sample size was calculated for an 80% statistical power, it is considered a small sample size (*n* = 45 eyes). Also, procedures will be done by a single surgeon, and thus the results cannot be generalized. Moreover, the follow-up will not be masked for the investigator, since gonioscopy would identify the procedure used in that patient.

In summary, our study provides a standardized protocol that could be replicated in future studies investigating various types of MIGS. This would allow comparison between different techniques in terms of efficacy, safety, and patients’ quality of life.

## Trial status

This is the third version of the protocol. The original study was approved in December 2021. The first amendment was approved in February 2022 (inclusion of Hospital Regional de Divinolândia as a participant center) and the second in July 2022 (inclusion of [name] in the study team).

The trial is in the recruitment phase. Recruitment started in March 2022 and is expected to be completed in March 2024.

## Data Availability

The datasets used and/or analyzed during the current study are available from the corresponding author on reasonable request.

## Abbreviations

MIGS: Minimally invasive glaucoma surgery
BANG: Bent ab interno needle goniotomy
GATT: Gonioscopy-assisted transluminal trabeculotomy
RCT: Randomized clinical trial
IOP: Intraocular pressure
POAG: Primary open-angle glaucoma
ReBEC: Registro Brasileiro de Ensaios Clínicos
OCT: Optic coherence tomography
BCVA: Best corrected visual acuity
RNFLT: Retinal nerve fiber layer thickness
KDB: Kahook Dual Blade
